#### AIM 1 Calculations

The sample size calculation is based on recent data on viral load suppression. This intervention is designed to support adolescents to manage their HIV as they transition into adulthood to achieve healthy outcomes, with viral suppression being the strongest outcome measure that is feasible. Viral suppression is a key health outcome we aim to achieve and maintain through the transition process and is of particular importance as ADCH program data has indicated that only 50% of 15-19 year olds are virally suppressed, with 50% having viral loads of 1,000 copies/ml or greater. With group sample sizes of 144, we will have over 85% power to detect a difference of 20% (an increase from 50% to

---

 Data are from ADCH’s routing VL screening, which is being conducted among adolescents who had been on cART for a minimum of 6 months, although many have been on cART for years.

70%) between the proportions virally suppressed in the intervention versus the control arms at the six-month data collection point, with Type 1 error of 5%, and 20% loss to follow-up. The team will also explore differences in self-reported adherence among the two study arms, with adherence assessed using a 30-day and 48-hour treatment gap measures that we have used in our previous research. Adherence is a proxy for achieving viral suppression. Adherence is also one of the toolkit module topics and maintaining adherence is a criterion for transition in the readiness to transition checklist.

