### **AIM 2 Calculations**

By conducting IDIs with about 40 youth sampled on VL test result (e.g. have VL failure at baseline and suppression at midline) and 40 sampled based on VL test result and varying experiences of violence, the IDIs should reach saturation on key themes while being able to stratify responses by sex, age, whether the youth transitioned, and clinical setting

The caregiver sample size will be about 30. With 30 IDIs, we should reach saturation across caregivers with differing degrees of involvement in the program. In addition, all health providers (estimated to be 10) who have a significant involvement with the intervention, all peer mentors (estimated to be 12), and all study staff (estimated to be 6) who have a significant involvement in the implementation of the referral process will be invited to participate in an IDI to capture the full experience of intervention implementation from these perspectives.

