present) will meet with the healthcare provider to discuss and answer any questions the caregiver may have about the youth's HIV self-management.

After this introductory meeting, the peer mentor and youth participant will meet every month for one-on-one meetings in or near the health facility for the duration of the six-month intervention. In these one-on-one meetings, the peer mentor will use the toolkit to guide and monitor the youth's movement along the transition continuum and assess the youth's ability to self-manage his/her HIV. Each participant may interact with the toolkit materials in unique ways -- it is intended to be used as a resource, rather than a set curriculum. Peer mentors may recommend additional visits with the youth participant, as needed.

To augment this approach, youth participants will also have access to monthly youth group meetings, facilitated by peer mentors, as well as have the option to invite a caregiver to up to three caregiver group meetings over the six-month intervention period.

There will also be specific intervention components for those youth (between the ages of 15 to 24 years) preparing to move from the pediatric/adolescent clinic at ADCH to the adult HIV clinic at NTH. Once a participant is assessed by clinic staff to be ready to transition to the adult setting, they will undergo two preparatory visits at the adult clinic. First, they will visit NTH to tour the facility and meet NTH YPMs and clinic staff. Second, newly transitioned youths will also have the option to have a YPM or other familiar health staff member attend their first two visits to NTH with them to ease the transition.

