### **Aim 1 & Sub-Aim 1A Quantitative Analyses**

The primary analysis to assess impact will use generalized estimating equation (GEE) (22) to compare the intervention to the comparison arm on VL suppression. This process will also be used to examine other key outcomes over time, such as self-reported medication adherence and internalized stigma.

This approach accounts for within subject correlations due to repeated measures. We will use GEE models with appropriate link functions (e.g., identity for continuous data, logit for binary data) and variance functions (e.g., identity for continuous data, logit for binary data) and variance functions (e.g., normal for continuous data, binomial for binary data). Unstructured working correlation matrices will be used in all models. The primary outcome will be cART adherence as measured by viral load suppression  $\leq 1,000$  copies/mL. In the stratified analysis (aims 1A), the models described above will be fit separately to two sub-samples of study participants – those participants who started the intervention in a pediatric care setting (i.e. ADCH) and those participants who started the intervention in an adult care setting (i.e. NTH, Twapia Clinic, and Lubuto Clinic). We will also examine pre- and post-intervention effects, and if outcomes change over time, at the 6-month and 12-month follow-ups. Secondary outcomes will include adolescents' transition status, including how many adolescents physically transitioned to adult care from the children's hospital.

Descriptive statistical methods will be used to assess the feasibility and acceptability of the intervention. The study team will also analyze attendance and the reasons for missed sessions. Together these data will provide valuable information on the feasibility of the intervention and participant exposure to intervention elements.

Finally, secondary data analyses will be carried out on participants' reported experiences of violence victimization. Descriptive statistics will be used to obtain weighted estimates of the youth's

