#### *Randomization description*

After baseline data collection, study participants will be randomized in 1:1 allocation ratio to receive either peer-mentoring intervention or usual care. Stratified randomly permuted block randomization (block sizes 4 and 6) will be used to generate the randomization scheme. Blocking will facilitate balanced allocation between the intervention arms, and random block size will reduce predictability of the group assignment. Randomization will be stratified by site and by gender, within site, for a total of 16 strata. Random allocation list will be generated, separately for each stratum, using 'ralloc' command (23) in STATA statistical software (24). The total sample size is 288 adolescents, but 380 random allocations are created (on average 38 per stratum) to account for potential allocation mistakes or discontinuations. If males are difficult to recruit more random allocations may be generated for females to make sure to reach the total sample size needed.

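### The primary GEE and the power statement make no allowance for clustering by peer mentor in the intervention arm, so the 6-month standard error is too small if mentors differ and the stated power is not assured

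*Protocol*

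**What the plan says.** - **Analysis.** Protocol V.C.4 (Aim 1 & Sub-Aim 1A Quantitative Analyses) specifies a GEE for viral suppression and states: "This approach accounts for within subject correlations due to repeated measures". It adds that every model will use an unstructured working correlation. With three visits per participant, that is a structure for repeated measures within a person. No mentor or session-group level is named.
- **Sample size.** Protocol III.B (AIM 1 Calculations) states "With group sample sizes of 144, we will have over 85% power to detect a difference of 20" percentage points. The assumed suppression rates at six months are 50% under usual care and 70% under the intervention. The error rate and attrition allowance read "with Type 1 error of 5%, and 20% loss to follow-up". It gives no ICC or design effect.
- **Delivery.** In V.C.1 (Intervention), "the peer mentor and youth participant will meet every month for one-on-one meetings in or near the health facility" for six months, and mentors also run monthly youth groups. The number of mentors appears in III.B (AIM 2 Calculations): "all peer mentors (estimated to be 12".
- **Allocation.** In V.C.5 (Randomization description), "study participants will be randomized in 1:1 allocation ratio to receive either peer-mentoring intervention or usual care". Under V.C.1 (Random Assignment; Second Intervention Period), the comparison arm has usual care until the 6-month data are in, and then receives the same programme.

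**The concern.** At the primary time point the design is partially nested: intervention youth are grouped under mentors and comparison youth are not. The protocol gives reason to expect mentors to differ. Each mentor assesses the youth's circumstances, draws up an individual action plan, chooses which toolkit topics to cover and may suggest extra visits. The common training of about two weeks may narrow these differences but cannot be assumed to remove them.

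If outcomes of youth who share a mentor are correlated, the intervention-arm proportion varies more than independent sampling implies. A GEE clustered on participant does not see that extra variance. The error runs in the anti-conservative direction: the confidence interval for the trial's main hypothesis is too narrow, and the power statement is optimistic.

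**Working it through.** **Inputs from the protocol.** 144 per arm; 50% against 70% suppressed at 6 months; 5% type I error; 20% loss; about 12 mentors.

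**Assumptions.** Two-sided test (sidedness is not stated); one mentor per youth; equal caseloads; ICC of 0.02, 0.05 or 0.10, because the protocol gives none.

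**Step 1: the protocol's own figure.** Analysed per arm: 144 × 0.8 = 115.2, taken as 115. The pooled normal approximation for two independent proportions gives:

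- null SE = √(2 × 0.6 × 0.4 / 115) = 0.0646
- alternative SE = √((0.25 + 0.21) / 115) = 0.0632
- power = Φ[(0.20 − 1.96 × 0.0646) / 0.0632] = Φ(1.16) = 87.7%

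The stated figure of over 85% is therefore reproduced under independence. A continuity correction gives 84.7%.

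**Step 2: design effect in the intervention arm.** Analysed youth per mentor: m = 115 / 12 = 9.6. DE = 1 + (m − 1) × ICC. The comparison arm keeps DE = 1.

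**Step 3: power.** Power = Φ[(0.20 − 1.96 × √(0.24 / 115 × (1 + DE))) / √(0.25 / 115 + 0.21 × DE / 115)].

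For example, at ICC 0.05: DE = 1.43, null SE = 0.0712, alternative SE = 0.0692, and power = Φ[(0.20 − 0.1396) / 0.0692] = Φ(0.874) = 80.9%.

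**Step 4: effect on the test if clustering is ignored.** With zero average effect, true SE / reported SE = √((1 + DE) / 2), and type I error = 2 × [1 − Φ(1.96 / that ratio)].

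| Assumed ICC | DE | Power | True SE / reported SE (null) | Type I error |
|---|---|---|---|---|
| 0 | 1.00 | 87.7% | 1.00 | 5.0% |
| 0.02 | 1.17 | 85.0% | 1.04 | 6.0% |
| 0.05 | 1.43 | 80.9% | 1.10 | 7.5% |
| 0.10 | 1.86 | 74.3% | 1.20 | 10.1% |

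Power reaches 85% at an ICC of about 0.02 and 80% at about 0.057.

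**Step 5: sensitivity to the number of mentors.** With 8 active mentors (m = 14.4), power at ICC 0.02, 0.05 and 0.10 would be 83.5%, 77.1% and 67.5%.

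These figures use normal quantiles. A t reference with about 11 degrees of freedom, or unequal caseloads, would lower power further.

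**The case against.** The strongest reply is that this is an omission from a brief analysis plan. The quoted sentence is true, it does not say that the participant is the only level, and a separate statistical analysis plan (not available here) could add mentors. This stands only in part. The protocol names the correlation handled and fixes an unstructured matrix for all models. That suits three visits within a person and is not workable for mentor groups of about ten youth. Followed as written, the plan leaves mentor variance out.

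Other points do limit the claim:

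- **Power.** A reader might infer that the stated power is wrong or not delivered. The protocol does not support that. The figure is right on its own inputs, and any shortfall depends on an ICC that is not given.
- **Type I error.** A reader might infer that the test exceeds 5% regardless. Youth are randomised individually, so if the programme affects no one, mentors add no variance and the comparison is valid. The inflated rates apply to a null of zero average effect with mentor effects that vary, the mentors being viewed as a sample of possible mentors.
- **Structure.** The figure of 12 is an estimate given for the interviews. One mentor per youth and equal caseloads are not fixed in the text.
- **Offsets.** Randomisation is stratified by site and gender, so any part of a mentor ICC that is really site variation does not inflate the arm contrast. Baseline suppression as a covariate could recover precision. At an assumed baseline-to-6-month correlation of 0.4 the variance factor is 1 − 0.4² = 0.84, against (1 + 1.43) / 2 = 1.21 at ICC 0.05, so the product is about 1.02. That helps power but does not correct a standard error that ignores mentors.
- **The violence analysis.** A reader might see an inconsistency because V.C.4 allows for same-clinic correlation there. That is an observational association, whereas the primary contrast is randomised within clinic. It is not evidence of a contradiction.

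**Conclusion.** The point holds in conditional form. The primary GEE accounts only for within-participant correlation, and the power calculation assumes independent participants, in a design that is partially nested by mentor up to the 6-month endpoint. If mentor effects vary, the standard error is too small, by the ratios tabulated above for ICCs of 0.02 to 0.10.

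The stated power is correct without mentor clustering but not assured with it: it is used up at an ICC of about 0.02 and is about 74% at 0.10. All of these figures rest on an assumed ICC, net of site differences, and on 12 mentors, one mentor per youth and equal caseloads. They exclude both the loss from a small-sample correction and any gain from baseline. Severity: should-fix.

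**What to change.** 1. Record each participant's assigned mentor.
2. For the primary 6-month comparison, specify a marginal logistic GEE with baseline viral suppression as a covariate. Use robust variance clustered on mentor in the intervention arm, with each comparison participant as a cluster of one, and a small-sample correction suited to about 12 mentor clusters.
3. State separately that by 12 months both arms are nested in mentors, and how the 12-month models handle this.
4. Keep the sample size. Restate power as 87.7% with no mentor clustering, and about 85%, 81% and 74% at ICCs of 0.02, 0.05 and 0.10, with the assumptions given.

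**Cost.** One data field, analysis wording, a somewhat wider interval and a less favourable stated power; no extra participants. Mentors already document each session and keep a folder per participant, so the field may be recoverable. Clustering in one arm only would also reveal to the analyst which of the coded groups is the intervention, so the model code should be fixed before the outcome data are opened.

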After the completion of the initial 6-month intervention and the subsequent 6-month follow-up assessment among participants in both arms, the primary intervention group will enter a maintenance phase and the comparison group will receive the intervention for six months. Assessments, including a survey and a blood draw for VL testing, will occur at baseline, at the end of the first six months, and at the end of 12 months (see Figure 1 under study implementation). Resistance testing will also be conducted at baseline for those participants who have a VL failure, defined as 1000 copies/ml or higher. Resistance testing is critical for this study as the primary outcome is viral suppression, something that will not occur if a participant has a resistant strain and is not on the correct treatment, no matter how adherent s/he may be. Routine VL results from among ADCH patients reveals that approximately 50% of adolescents have VL failure. Based on that data, we estimated that 50% of the 288 participants in this research (n=144) will have VL failure and need resistance testing.

At the end of the initial 6-month intervention, we will begin conducting qualitative in-depth interviews with participants, their caregivers when possible, and the health care providers, peer mentors, and study staff involved in delivering the program. These data will provide contextual details and experiences to help interpret the study findings and determine what aspects of the intervention were valued.

- B. Provide a sample size and a justification as to how you arrived at that number. If you use screening procedures to arrive at a final sample a table may be helpful.

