## **Contacting Participants**

Study staff will contact all participants who do not attend a planned study or intervention visit. As part of routine care the clinic staff conducts home visits for YLHIV who have missed appointments to re-engage them in care. The research study will follow similar procedures if a participant misses a study visit. First, attempts will be made to contact the missing participant through the phone numbers and contacts provided during enrollment. During study enrollment, the research team will confirm the appropriate phone numbers and phone ownership (in an earlier study among this population, 69% of 309 youth use cell phones). The team will also request permission to contact the youth's caregiver, or the caregiver's contact, to inquire about the missing participant as well. If the missing participant cannot be reached the trained study interviewers will go to the home to inquire. At the home, the study staff will inquire about the youth using a script, but will not discuss the research study or disclose the youth's participation. If no one is home or they are asked to follow-up later, they will attempt to reach the participant three times before considering the participant lost to follow-up. This process has received approval from the Zambia and Hopkins IRBs for previous studies and has worked well. Participants lost to follow-up will not be replaced in the study.

3. Describe the expected duration of the study from the perspective of the individual participant and duration overall.

The official study period is from May 15, 2016 to June 30, 2019. From a participant's perspective, the overall duration will be about 18 months – 2 months for recruitment and baseline data collection, 6 months for the initial intervention, 2 months for midline data collection, 6 months for the comparison group to receive the intervention and the initial intervention group to receive maintenance care and 2 months for endline data collection. However, recruitment and follow-up interviews between sessions may take less time.

4. Provide a brief data analysis plan and a description of variables to be derived.

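### The primary GEE does not commit to adjusting for site, gender or baseline suppression, or say whether baseline viral load is a covariate or a response; fixing this could add power at almost no cost

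*Protocol*

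**What the plan says.** In the Protocol's data analysis plan (V.C.4, Aim 1 & Sub-Aim 1A Quantitative Analyses) the method is stated as: "The primary analysis to assess impact will use generalized estimating equation (GEE) (22) to compare the intervention to the comparison arm on VL suppression". The model details follow: "We will use GEE models with appropriate link functions", matching variance functions, and "Unstructured working correlation matrices will be used in all models". The reason given for GEE is that "This approach accounts for within subject correlations due to repeated measures". The section then adds: "We will also examine pre- and post-intervention effects, and if outcomes change over time, at the 6-month and 12-month follow-ups". No covariate is named for the primary model, and no sentence says that the model is unadjusted. Aim 1a refits the same models separately for the children's hospital and for the three adult sites.

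Three other places bear on this:

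- **Randomization description (V.C.5.A):** "Randomization will be stratified by site and by gender, within site". The text gives the total as 16 strata.
- **Study design (III.A):** viral load is drawn from all participants at baseline. "Resistance testing will also be conducted at baseline for those participants who have a VL failure, defined as 1000 copies/ml or higher". Half of the 288 participants (144) are expected to need that test.
- **AIM 1 Calculations (III.B):** power is given as more than 85% for 50% versus 70% suppressed at six months, with 144 per arm, 5% type 1 error and 20% loss to follow-up.

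**The concern.** The sample size rests on one quantity, the difference between arms in the proportion suppressed at six months. The analysis text describes a repeated-measures model and does not tie it to that quantity. Two choices are left open.

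The first is the covariates. Baseline suppression is likely to predict 6-month suppression, and adjusting for a predictive baseline variable makes the comparison more precise without new data. Site and gender were used to balance the arms. If they predict suppression, an analysis that ignores them gives a standard error that is too large.

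The second is the role of baseline viral load. A repeated-measures GEE can take it as a covariate, as a response with a baseline mean common to both arms, or as a response with a free arm-by-time interaction. The first two use the baseline information to about the same effect. The third tests a change-from-baseline contrast, which is less precise than the plain 6-month comparison when the correlation is below 0.5. The stated power would then no longer describe the test performed.

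**Working it through.** **Inputs from the Protocol.** 144 per arm; 20% loss, so 144 × 0.8 = 115.2, taken as 115 evaluable per arm; 50% versus 70% suppressed; 5% type 1 error. Sidedness is not stated, so two-sided (1.96) is assumed.

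**Input not in the Protocol.** The correlation ρ between baseline and 6-month suppression. It is varied from 0 to 0.6.

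**Step 1: reproduce the stated power.**
- Variance sum: 0.5 × 0.5 + 0.7 × 0.3 = 0.46. Standard error: √(0.46/115) = 0.0632.
- Power = Φ(0.2/0.0632 − 1.96) = Φ(3.162 − 1.96) = Φ(1.202) = 88.5%.
- With the pooled variance under the null: Φ((0.2 − 1.96 × √(0.48/115))/0.0632) = 87.7%.

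Both agree with the stated figure, and neither uses a covariate.

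**Step 2: compare the analyses the text allows.** The approximate variance relative to the unadjusted 6-month comparison is 1 − ρ² for baseline adjustment and 2(1 − ρ) for an arm-by-time contrast. Power = Φ(3.162/√factor − 1.96).

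| ρ | 6-month, unadjusted | 6-month, baseline-adjusted | Arm-by-time |
|---|---|---|---|
| 0 | 88.5% | 88.5% | 60.9% |
| 0.2 | 88.5% | 89.8% | 70.5% |
| 0.3 | 88.5% | 91.2% | 76.2% |
| 0.4 | 88.5% | 93.2% | 82.3% |
| 0.5 | 88.5% | 95.5% | 88.5% |
| 0.6 | 88.5% | 97.7% | 94.2% |

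The arm-by-time contrast reaches 85% only when 3.162/√(2(1 − ρ)) is at least 1.96 + 1.036, that is when ρ is about 0.44 or more.

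**Step 3: check by simulation on the logit scale.** 115 per arm, 3,000 replicates, 50% suppressed at baseline, 50% versus 70% at six months. The association is set by an assumed odds ratio between baseline and 6-month suppression; ρ is its value in the comparison arm.

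| Odds ratio (ρ) | Unadjusted | Adjusted for baseline | Arm-by-time |
|---|---|---|---|
| 1 (0.00) | 88.9% | 88.6% | 60.8% |
| 3 (0.27) | 87.1% | 89.4% | 73.5% |
| 5 (0.38) | 87.7% | 91.4% | 80.4% |
| 10 (0.52) | 88.0% | 94.5% | 88.4% |
| 20 (0.63) | 86.8% | 96.6% | 93.7% |

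The two methods agree closely. Adjustment costs nothing beyond simulation noise when baseline is uninformative, and gains up to about 10 points when it is strongly predictive.

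**Step 4: what cannot be computed.** The Protocol gives no suppression rates by gender, none by site other than the children's hospital, and no resistance prevalence. No gain can be calculated for those factors.

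**Step 5: stratum count.** Four sites × 2 genders = 8, but the text states 16. The 380 allocations at an average of 38 per stratum imply 380/38 = 10. The three figures do not agree.

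**The case against.** The strongest objection is that silence is not a decision. The form asks the investigators to "Provide a brief data analysis plan and a description of variables to be derived", and a covariate list is commonly left to the statistical analysis plan, which is not at hand. This stands: the text never says that the model is unadjusted, and nothing in it contradicts the stratified randomisation. What remains is that the section already fixes the link, variance function and working correlation for all models. One more sentence there would settle the contrast at almost no cost.

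Several stronger readings are tempting, and the document does not support them.

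- **That the trial is underpowered.** The hypothesis and the sample size both target the arm difference at six months, and the unadjusted comparison meets the stated power. The arm-by-time figures describe a model that the text permits but does not specify.
- **That the standard error is wrong.** It is too large only if site or gender predicts suppression. The error would be conservative, and no rates are given from which to size it.
- **That loss to follow-up biases the unadjusted estimate.** Nothing in the document suggests that loss depends on baseline failure.
- **That resistance must be in the primary model.** It is tested only in those failing at baseline. The document ties its effect to being on unsuitable treatment, and under Communicating test results providers are told of resistance in both arms so that treatment can be reviewed. Its value as a predictor at six months is therefore uncertain, and the resistant group could be small.

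**Conclusion.** The point holds as a recommended improvement. The primary model is not tied to the 6-month contrast used for power, and it makes no commitment to use the stratification factors or baseline suppression.

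For baseline suppression the likely gain is about 3 to 9 points of power at a correlation of 0.3 to 0.6, and about 1 point at 0.2. If the effect were read as an arm-by-time term, the loss against the unadjusted comparison would be about 12 points at 0.3 and 6 at 0.4. These figures rest on 115 evaluable per arm, a two-sided 5% test, the planned 50% and 70%, and an assumed correlation. The benefit of site, gender and resistance is unquantified.

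**What to change.** In the Aim 1 analysis text, or in the statistical analysis plan before unblinding:

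1. Name the primary contrast as suppression at six months by arm.
2. Include site, gender and baseline suppression as covariates.
3. Report the standardised (marginal) risk difference with its confidence interval. An adjusted logit model otherwise gives a conditional odds ratio, which does not correspond to the 20-point difference used in the sample size.
4. Split baseline failure by resistance status only if the numbers allow, or as a sensitivity analysis.
5. First reconcile the stratum count, so that the model uses the factors that were actually used to randomise.

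The cost is slightly more analysis work and a few lines of text. The variables are already collected, and the sample size does not change.
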